**Fig. 1 Fig1:**
[figure not shown]
Intervention and data collection in the OTIS study

### Study products

All participants will be supplied with study products free of charge. In the ND group, these will be specially prepared, protein-reduced, age-adjusted milk cereal drinks (MCDs), baby cereals and baby milk and commercially available baby foods in glass jars (BIG). The control group will be offered commercially available, age-adjusted MCDs, baby cereals, baby milk and BIG. Semper AB, Sundbyberg, Sweden, will provide all products.

The participants will be provided a month’s supply of study product at baseline and subsequently the families will come to the Paediatric Research Unit to collect more products as needed but not more than for one month at a time.

### Introduction of complementary feeding

The switch from the liquid diet of the young infant to the mixed diet of the older infant or toddler is a gradual process. First, when the infant starts showing interest in other foods the parent or caretaker offers small taste portions of various simple foods to take benefit of the infant’s curiosity. These small titbits, in Sweden usually served as purees or mashes of various vegetables, are provided as a way to familiarise the infant to new flavours and consistencies of foods which the infant will eat in the future, but they contribute little to the total energy and nutrient intake of the infant, which at this time is covered by breast milk or infant formula. Later, as the infant grows and develops many parents start substituting one or more breast- or formula-feeds with more and more solid food.

The ND group will be given recipes for fruit, berries and vegetable purees and instructions how to prepare these recipes at home. The main ingredients will be fruits, berries and vegetables which grow and are available in the Nordic region [26]. The dishes will be given as small taste meals to the participating infant when the parents feel it prudent to start offering the infant other foods besides breast milk or formula and the infant is deemed ready by the parent. This time-point is to be chosen by the parents themselves. When the time has come for taste meals, the instructions to the parents will be that they should systematically introduce eight different fruits, berries and vegetables, each one given at least 3 times daily for three consecutive days whether or not the child immediately appreciates the flavour/consistency the first time. After the first 3 days, the parent will switch to another fruit, berry or vegetable until the different ingredients have been sampled. In total, there will be a maximum of 72 exposures during 24 days.

The control group will be given the standard, oral and written advice that is given from well-baby clinics to parents when beginning with small taste meals based on national guidelines [52].

### Study design and interventions

After recruitment the participating child will be randomized to either a regular (control) diet or the experimental Nordic diet (ND).

#### The Nordic diet group

The Nordic diet group will experience three interventions (Fig. 1): i) a systematic introduction of taste portions, ii) milk cereal drinks (MCD), porridge and baby milk with reduced protein content, and iii) homemade and industry manufactured (BIG), protein-reduced main meals with a predominance of Nordic ingredients.When the parents have made the decision that their child should start with complementary foods, the ND group will be given instructions to systematically introduce four different fruits and berries (apple, raspberry, buckthorn/lingonberry, cranberry) and four vegetables (green peas, cauliflower, turnip, daikon), each one given at least 3 times daily for 3 consecutive days whether or not the child likes the flavour/consistency the first time or not. In total, there will be a maximum of 72 exposures during 24 days.When the parents start to complement the baby’s diet with MCD and/or porridge, the participants will be given protein-reduced products. The families will be instructed to use these products at their own discretion and they will have an offer to continue with these study products for as long as the child remains in the study.When the child is ready for a larger variation in meals, the ND group will be given recipes for main meals (lunch, dinner) and BIG with predominantly Nordic ingredients. The families can use these recipes and BIG as they see fit, but we will recommend that the families use the recipes for home-made food at least once daily.

#### The regular diet group

The regular diet group will function as control for to the ND group (Fig. 1). The participants will be given the current advice on infant feeding issued by the Swedish National Food Agency [52]. They will also be given regular, commercially available MCD, porridge, baby milk and BIG. No advice or recipes for meals will be given apart from the current recommendations.

### Parental support

Parents with children in the ND group will be given support to continue following the dietary intervention. They will be invited to participate in a closed Facebook™ group. In this forum parents can discuss with a study dietician and among themselves, sharing experiences. Parents will also have instructional videos on the preparation of certain study foods available within the group setting. Participants in the group will share experiences and other information at their own discretion. No data will be collected through this group, but the group may function as a way to inform the families that participate in the group about upcoming study events and remind participants to send in questionnaires, etc.

Both the intervention and the control groups will get monthly telephone calls from a research nurse or a study dietician as part of the regular data collection (see below).

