### Adverse events

An adverse event (AE) is any undesirable medical occurrence in a subject administered a study product, regardless of its cause. An adverse event can therefore be any unfavourable and unintended sign (including an abnormal laboratory finding), symptom, or disease temporally associated with the use of a study product, whether or not considered related to the study product. All adverse events, including observed or volunteered problems, complaints, or symptoms will be recorded on the Symptoms registration form. Each adverse event is to be evaluated for duration, intensity, and causal relationship with the study product or other factors. The participants will be instructed to report any AE that they experience to the researchers through the Symptoms registration form and by contacting the researchers. The research nurse will assess AE at each visit, i.e. 9, 12 and 18 mo. of age and at all monthly telephone follow-ups and report to the principal investigator (TL).

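### The online group offered only to Nordic diet families creates a risk of unequal ascertainment of parent-reported outcomes, of unknown size and direction

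*Protocol article*

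**What the plan says.** *Parental support* opens with the ND arm: "Parents with children in the ND group will be given support to continue following the dietary intervention". The support is a closed online group to which these parents are invited. Study staff take part: "In this forum parents can discuss with a study dietician and among themselves, sharing experiences". On data the section states: "No data will be collected through this group, but the group may function as a way to inform the families". The same sentence goes on to allow the group to be used to "remind participants to send in questionnaires, etc". No equivalent group or reminder is described for the control arm.

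*Adverse events* sets the recording rule: "All adverse events, including observed or volunteered problems, complaints, or symptoms will be recorded on the Symptoms registration form". Parents are to report events "through the Symptoms registration form and by contacting the researchers". Staff also ask actively: "The research nurse will assess AE at each visit, i.e. 9, 12 and 18 mo. of age and at all monthly telephone follow-ups".

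The calls are common to both arms: "Both the intervention and the control groups will get monthly telephone calls from a research nurse or a study dietician". *Adherence*, *Symptoms registration* and *Procedures* have these calls cover study-related problems and check the symptom form, with no distinction by arm.

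**The concern.** Two features of the group apply to one arm only, and both concern what parents report.

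First, the dietician in the group is trial staff. Elsewhere the article has a nurse or dietician make the monthly calls. A rash or a feeding problem described to that dietician in the group is a volunteered problem under *Adverse events*, yet it arrives in a channel that *Parental support* declares free of data collection. No sentence joins the two rules. A parent who has already told the dietician may see less reason to enter the problem on the form.

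Second, a reminder posted in the group can reach only ND families who joined it. If it is used, prompting to return parent-completed material depends on the arm.

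The outcomes exposed are those that rest on parents' reports. Table 1 lists symptoms registration, allergy and atopic manifestations, eating behaviour, temperament and the developmental questionnaire outside the primary outcomes. If reporting or return differs by arm, part of any observed difference, or of any apparent lack of one, could come from ascertainment rather than diet. Analysis cannot recover an event that was never entered.

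**Working it through.** The article gives no adverse-event rate, form-return rate or capture rate, so the size of the effect cannot be derived. The check sets the sections side by side, with an illustration on assumed values.

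**Routes by which a problem can reach the record**

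| Route | ND arm | Control arm | Source |
|---|---|---|---|
| Symptom form, returned monthly and checked at the monthly follow-up | yes | yes | *Symptoms registration* |
| Contacting the researchers | yes | yes | *Adverse events* |
| Monthly call | yes | yes | *Parental support*, *Adherence* |
| Visits at 9, 12 and 18 months | yes | yes | *Adverse events* |
| Online group with dietician | by invitation; not a data channel | none described | *Parental support* |
| Reminder through the group | possible | none described | *Parental support* |

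The first four rows are equal by design. Only the last two differ.

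**Do the two rules conflict?** They meet without a connecting instruction. The data rule concerns collection through the group. It does not prohibit entering the same problem on the form, and the recording rule has no exemption for the group. Both can be met if the dietician refers the parent to the form or the nurse, but the article does not say that this happens.

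**How far do the shared routes close the gap?** To be lost, a problem must be raised in the group, left off the form, and not mentioned at the next call or visit. That narrows the risk without removing it. *Procedures* lists calls at 7-8, 10-11 and 13-17 months, while baseline falls at 4-6 months. A child enrolled at 4 months could therefore finish the 24-day food introduction before the first call listed there, although *Adherence* speaks of monthly contact without that gap.

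**Direction.** Problems settled in the group and not entered would lower the ND count. Extra prompts would raise ND return. The net sign cannot be determined.

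**Illustration (all values assumed).** Let p be the true proportion with an event, equal in both arms, and let c1 and c0 be the capture proportions. The spurious difference is p × (c1 − c0).

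- p = 0.30, capture 0.95 versus 0.85: 0.285 − 0.255 = 0.03.
- p = 0.50, same capture: 0.475 − 0.425 = 0.05.
- Capture reversed: −0.03 and −0.05.

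With 100 evaluable children per arm (125 × 0.80), a two-sided 5% test of proportions would be significant in the direction of the artefact with probability about 0.07 and 0.105 respectively, against 0.025 with no artefact. At this size the artefact would more often shift an estimate than produce a false significant result.

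**Sample size.** The figure in *Power calculation and statistical analyses* reproduces: n = 2 × (1.960 + 0.842)² × 0.6² / 0.24² = 2 × 7.849 × 6.25 = 98.1, so 99 per group (two-sided test assumed). Then 99 / 0.80 = 123.75, so 124, against 125 stated. Nothing in this calculation depends on the online group.

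**The case against.** The strongest reply is that the sections do not contradict each other. The data rule defines the group as a support channel, and the duty to record every event stands unaltered. Capture is active and the same in both arms. The reminder is only something the group may do, symptom forms are not named, and the article does not say that controls get no reminders. Control families can also settle problems outside the trial, for instance at the well-baby clinic. How remarks in the group are passed on could sit in the full protocol or in staff instructions.

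Much of this stands, and it rules out several stronger readings that a reader might infer:

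- *That problems raised in the group are barred from being recorded.* The text does not say so.
- *That adverse-event capture does differ by arm.* This does not follow, because the main routes are identical and the two mechanisms pull in opposite directions.
- *That every one of the 125 ND families is affected.* Families are invited, and the number who join is not given.
- *That unequal reminders reach the fat-mass result*, because repeated non-adherence to symptoms registration is an exclusion criterion. This needs several assumed steps, and the reminder text does not name the symptom form.

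Two things remain. The arm-specific reminder channel is a stated feature of the plan, not a detail left out by condensation. And the article itself places trial staff and a no-data rule in the same channel. A clinic outside the trial is not comparable, because its staff are not the people to whom the recording rule applies.

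**Conclusion.** The point holds as a risk of unequal ascertainment of parent-reported outcomes, not as a demonstrated bias or a flat contradiction. It has two sources: a reminder channel that can reach only participating ND families, and the missing link between what parents tell the dietician there and the duty to record it.

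Its size and direction are unknown. The 3 to 5 percentage points above rest wholly on assumed event and capture proportions and show scale only. The conclusion assumes that the group is used for reminders without a matching prompt to controls, or that some problems raised there go no further. The article permits the first and does not exclude the second.

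The exposed outcomes are adverse events, symptoms and the parent-completed questionnaires. The primary fat-mass comparison rests on deuterium dilution and is not affected. The point is modest and merits correction mainly because correction is so cheap.

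**What to change.** 1. Do not use the group for reminders about forms or questionnaires. Alternatively, send the same reminders on the same schedule to both arms by a shared channel, such as the monthly call.
2. Reconcile *Parental support* with *Adverse events* by stating that any health or feeding problem raised with the dietician in the group is referred to the adverse-event reporting route and entered with its source marked.
3. Base the arm comparison of adverse events and symptoms on sources that both arms share (form, calls, visits), and list events known only through the group separately.
4. Report the return of forms and questionnaires by arm.

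The cost is a sentence or two of protocol text, an instruction to the dietician, a source field on the record and slightly more reminder work. *Trial status* has recruitment closed in February 2018 and data collection running to February 2019, so items 1 and 2 can apply only to the follow-up that remains. Item 4 can still be done afterwards, and so can item 3 where the source of an entry can be established.

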### Data collection

Main data collection points will be at baseline, i.e. when the child is between 4 and 6 mo. of age, and at 9, 12 and 18 mo. of age. At these time-points, the participants will come to the Paediatric Research Unit for measurements and sampling (Fig. 1). Questionnaires and forms will be available electronically or on paper. Electronic questionnaires will be administered through Texttalk Websurvey, a tool provided by Umeå University for electronic surveys. The questionnaires and forms will be filled out prior to the main data collection points. Questionnaires on paper will be collected at these times. All forms, either electronic or paper will be checked for completeness at the time when they are returned to the researchers. Incomplete or possibly erroneous data will be double-checked with the participating families through telephone follow-up. All data will be entered and stored electronically in a secure database provided by Umeå University. Paper copies of questionnaires and measurement protocols will be stored in accordance with University rules in a safe archive to which only researchers and administrative staff at Paediatrics, Department of Clinical Sciences has access.

#### Sociodemographic data

At baseline, information will be collected on family size (number of sibling, household structure), living conditions, country of birth, parental education, occupation and smoking habits, chronic diseases in the family history (allergies, atopic diseases, diabetes type 1 and 2, obesity, hypertension, stroke, cardiovascular disease, cancer), details on the birth of the participating child (including a request to collect the birth document from the mother’s health record), and the health and feeding pattern since birth of the participating child.

#### Adherence

The research nurse or dietician will contact the participating families monthly by telephone to check adherence to the protocol, study related problems, consumption and supply of study products and the symptoms registration form. Data from the telephone interview will be registered electronically.

#### Anthropometry and blood pressure

Anthropometric measurements will be taken at baseline (4–6 mo. of age), 9, 12 and 18 mo. of age at the Paediatric Unit (Department of Clinical Sciences, Umeå University, Umeå, Sweden) by experienced paediatric research nurses in accordance with standardized procedures [53]. Nude weight will be measured to the nearest 0.1 kg with electronic baby scales (Seca 727, Bromma, Sweden). Recumbent length will be measured to the nearest 0.1 cm with a paediatric length board (CMS Weighing Equipment Ltd., London, UK). Head circumference will be measured to the nearest 0.1 cm with non-stretchable tape for infants (Seca 212, Germany). All measurements will be taken in triplicate and the mean value will be recorded.

Blood pressure will be measured with the child sitting in the parent’s lap at baseline (4–6 mo. of age), 12 and 18 mo. of age using a Carescape Dinamap V100 monitor (GE Healthcare AB, Sweden) and age-appropriate blood pressure cuffs.

At baseline, the weight, height and blood pressure of the parents will be measured.

#### Body composition

Total body water (TBW) as a measure of body composition (3 compartments model including total body water, fat and fat-free mass) will be determined at 12 and 18 months of age. TBW will be assessed using deuterium (^2^H_2_O) according to the procedure advised by the International Atomic Energy Agency [54] in collaboration with the MRC Human Nutrition Research Laboratory, Cambridge, UK. A pre-dose urine sample will be collected by placing an absorbent pad (Bastos Viegas, Penafiel, Portugal) in the diaper of the infant. Each infant will then be given an oral weighed dose of deuterium of 1 g/kg. Post-dose urine samples will be collected at home once daily for five consecutive days with dates and times recorded for all samples using absorbent pads as described above, omitting the first urine portion of the day. Each collected pad will be stored at − 18 °C. The pads will then be taken to the Paediatric research facility at Umeå University Hospital, thawed and the urine content extracted using a press, collecting the urine in glass bottles. The glass bottles will be stored at − 20 °C until transported to MRC Elsie Widdowson Laboratory, Cambridge, UK for analysis.

#### Dietary intake, eating behaviour and food acceptance

Dietary intake will be assessed using a 5-day food record. This methodology has been extensively used in this age group by the researchers [7, 55]. On four occasions, at baseline (4–6 mo. of age), 9, 12 and 18 mo. of age, the parents will be asked to register the participating child’s intake of foods and drinks during consecutive 5 days. Parents will be instructed how to use record sheets and household measures to quantify and describe their infant’s dietary intake. Previous research has found that parents tend to underestimate energy intake in this age group using only food records [56]. In order to improve estimates of energy and nutrient intake, the parents will also be asked to photograph the child’s meal portions during the 5-day food record, just before the meal is served and right after, taking 2 photos each time from perpendicular angels. The parents will send the photos electronically to a study-specific cloud service provided by Umeå University. In a separate sub study, this methodology will be validated using doubly labelled water.

Eating behaviour will be assessed by three recently validated, Swedish questionnaires, the Children’s Eating Behaviour Questionnaire (CEBQ) [57], the Child Feeding Questionnaire (CFQ) [58] and the Covert and Overt Control Questionnaire (COC) [59]. The questionnaires will be administered in electronic form (Texttalk Websurvey), the CEBQ together with the 5-day food record and the CFQ and COC at baseline.

A videotaped test meal to assess food and taste acceptance will be administered at 12 and 18 mo. of age. The video recording will take place in the home of the participant. During the meal, the parent will serve a prepared study meal (fruit-flavoured yoghurt, fruit-flavoured milk and a cracker with a vegetable spread) to the child. The meal will be videotaped and later assessed for acceptance in collaboration with associate professor [name], Karolinska Institute, Stockholm, Sweden.

#### Biochemical data

Venepuncture blood samples will be collected at baseline (4–6 mo. of age), 9, 12 and 18 mo. of age. Samples will be collected by experienced paediatric research nurses at the Paediatric Research Unit (Department of Clinical Sciences, Paediatrics, Umeå University, Umeå, Sweden). A local anaesthetic cream will be applied prior to blood sampling. The total collected blood volume will be less than 3 ml/kg per 24 h [60]. Blood for immediate analysis (complete blood count, iron status, P-urea, hsCRP) will be taken off and sent to the Department of Clinical Chemistry, Umeå University Hospital. The remaining blood will be centrifuged, the plasma removed and frozen at − 80 °C until further analyses. At baseline, blood will be collected from the parents for analyses of iron status (complete blood count, serum (S-) ferritin, S-Fe and S-transferrin) and metabolomics. Urine will be collected by placing an absorbent pad (Bastos Viegas, Penafiel, Portugal) in the diaper of the infant at baseline (4–6 mo. of age), 12 and 18 mo. of age for analyses including metabolomics, lipidomics and oxidative status. The urine will be stored at − 20 °C until further analyses. Metabolomics and lipidomics will be done in collaboration with the Swedish Metabolomics Centre, Umeå and prof. [name], Department of Nutrition, University of California, Davis USA (our group collaborates with both platforms). Any remaining blood or urine will be stored in the Biobank of the Department of Clinical Sciences, Paediatrics, Umeå University, Sweden.

